**Treatment schedules**

**Duration and Frequency**

- Patients will be treated only as outpatients.
- Outpatient treatment shall be once a month for six months, with evaluation in the seventh month.
- In principle, the oral medication will be continued.

**Interventions**

The patients are randomized to receive the AKA-H method or the sham technique. The AKA-H method is applied once a month for 6 months to the sacroiliac joint for treatment of low back pain using the following techniques: 1) upward gliding, 2) downward gliding, 3) superior distraction, and 4) inferior distraction.

- **Sham technique:** During the sham technique, the patient lies sideways with both hips and knees extended (each joint is close-packed), and the therapist stands on the ventral side of the patient. The therapist’s thumb, on the cephalic side of the patient, is placed on the S1 spinous tubercle, giving a light downward force while the index finger of the therapist’s other hand is placed underneath the S1 spinous tubercle to counteract the downward force; thus, the sacroiliac joints do not actually move. The same procedure is performed in which the therapist’s thumb, on the caudal side of the patient, is placed on the S3 spinous tubercle with the index finger of the therapist’s other hand underneath it. This procedure is slowly repeated twice with the procedure on S1 first, followed by S3, alternately.

**Change criteria: Combination therapy**

- If patient so wishes, a disclosure is given immediately, and Sham procedure can be changed to AKA-H method. A combination treatment is possible, with continuous administration of both the oral medicine and the analgesic patch.
- In the event that lower back pain ceases completely, and that patient does not wish to have treatment, this constitutes a complete recovery. In the event that patient wishes to terminate treatment or if deterioration of general condition of patients or the presence of an illness involving the vital prognosis is suspected, therapy is suspended immediately, and a thorough examination and appropriate treatment is performed.

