**3. Study Design**

・Using a random number table created by free-software R (http://www.r-project.org), the patients were randomly assigned to the AKA-H (AKA-H) or the sham (S) groups.

・This study was a parallel group comparison in which the AKA-H group and S group were compared for 6 months. The study was randomized at the level of the individual patient, and it was a single-blind RCT in which only the patients were blinded to the details.

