**Sampling and Recruitment**

AKA-H has been widely known among patients in Japan through mass communication or personal communication and is expected to be referred from home doctors. A list of hospitals where AKA-H is available is shown on the website of the Japanese Medical Society of Arthrokinematic Approach(http://www.aka-japan.gr.jp). Doctors listed there are specialists or advising doctors who have passed an exam stipulated by the Society. When patient desires treatment by AKA-H, he/she will be required to call Saitama Prefectural Rehabilitation Center first, and will be asked his/her address, phone number, and age by a Center staff. Then, the first author will contact him/her by phone within 3 days to give a full explanation of the RCT. If the patient shows his/her willingness to participate in the study, he/she will receive an email with instructions on the AKA-H procedure, consent form, treatment flow at the first visit, specially created calendar type form to record VAS scores, and a scale to measure VAS.

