**・Randomization**

Output 0 or 1 in order using a random number table created free-software R (for example, 0 for the first person, 1 for the second person, and 1 for the third person). A piece of paper with 0 on it is enclosed in an envelope with 1 on it, and the envelope is sealed. A piece of paper with 1 on it is enclosed in an envelope with 2 on it, and then the envelope is sealed. This procedure will be done by a nurse in the outpatient department. The nurse will keep and store the envelopes without being informed of the purpose of creating those envelopes so that the first author cannot be involved in the randomization. At the patient’s first visit, a nurse will bring an envelope with the number corresponding to the patient number to the first author after the patient walks in the outpatient medical examination room. Then, the first author opens the envelope to provide sham procedure or AKA-H after confirmation of the number without informing the patient. Caution is needed to have the patient not recognize which procedure will be performed.

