**Post-Treatment Therapy**

Once the test is complete, disclosure is made to the patients as to whether they had AKA-H treatment or Sham treatment, and patients are asked if they wish to continue treatment. If treatment was Sham, patients were allowed to change treatment to AKA, and if treatment was AKA-H, patients could continue with AKA-H.

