**5. Outcomes and Confidentiality**

Primary outcome and secondary outcomes

- Primary outcome is mean VAS score over a month from the previous visit.
- Participants are required to record their VAS score in a form every day at almost the same time for at least 1 month until the first visit and bring the recorded form along with consent form at the first visit.
- Secondary outcomes are Roland-Morris Disability Questionnaire (RDQ) and 36-Item Short-Form Health Survey (SF-36).
- Participants will fill RDQ and SF-36 at every visit including the first visit at the waiting room by advance reservation only before seeing a doctor. Participants are required to visit the outpatient office once a month, in principle, for 6 months after initiation of treatment.
- A VAS record form will be collected at every visit, and a new one will be provided to the participants.
- RDQ and SF−36 will be filled at the waiting room and will be collected at every visit. Those collected record forms will be stored in the locked locker at outpatient department.

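### Disclosure on request, and change from sham to AKA-H, is open during the six-month comparison although both are already offered afterwards

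*Protocol*

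**What the plan says.** Protocol section 4, Change criteria: Combination therapy, reads: "If patient so wishes, a disclosure is given immediately, and Sham procedure can be changed to AKA-H method". It gives no minimum time on treatment, no lack-of-response criterion and no safety trigger. The next item under that heading deals with complete recovery, and with suspending therapy at the patient's wish or on deterioration.

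Post-Treatment Therapy deals with the end of the trial: "Once the test is complete, disclosure is made to the patients". Sham patients may then move to AKA-H, and AKA-H patients may continue.

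Other relevant provisions:

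- **Blinding (section 3):** "it was a single-blind RCT in which only the patients were blinded to the details". The Randomization text adds: "Caution is needed to have the patient not recognize which procedure will be performed".
- **Schedule (Duration and Frequency):** "Outpatient treatment shall be once a month for six months, with evaluation in the seventh month".
- **Outcomes (section 5):** "Primary outcome is mean VAS score over a month from the previous visit". The VAS diary, RDQ and SF-36 are all completed by the patient.
- **Recruitment (Sampling and Recruitment):** the process starts "When patient desires treatment by AKA-H".
- **Analysis (section 6):** intention-to-treat, last observation carried forward for missing data, and a two-way repeated measures analysis of variance.

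**The concern.** With an unblinded therapist and patient-reported outcomes, the comparison relies on patients not knowing their arm. Sealed envelopes protect allocation, and diaries kept between visits limit the therapist's influence on ratings. Neither restores a blind that has been lifted.

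The clause lets any patient in either arm lift it at any time. The change of treatment is one-sided, from sham to AKA-H, and the patients recruited are those who came asking for AKA-H. Whether a patient asks may depend on how they are doing, so disclosure need not be random or balanced between arms. An analysis plan could choose how to handle data after a disclosure, but it could not re-blind anyone.

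**Working it through.** The Protocol has no figure to reproduce on this point. It gives no switching rate, effect size, standard deviation or sample size. The check is therefore textual, followed by an illustration.

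**Step 1: when the clause applies.** The change criteria do not say in so many words that they operate during the six months. Three things point that way: the heading, the promise that disclosure is immediate, and the separate rule for what happens on completion. If the clause covered only the period after completion, it would repeat Post-Treatment Therapy.

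**Step 2: what happens to the data.** The Protocol does not say whether a patient who is told the arm, or who switches, stays in follow-up. The general rule in section 5 favours continued collection ("A VAS record form will be collected at every visit, and a new one will be provided to the participants"), but it does not address this case. There are two branches:

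- *Follow-up continues.* Disclosed patients in either arm rate pain, disability and health status knowing their allocation. Switched sham patients receive AKA-H but count as sham under intention-to-treat, which pulls the contrast towards no difference.
- *Follow-up stops.* There are no unblinded ratings and no dilution, but section 6 fills the later months with the last value. If patients ask at a bad point from which they would have recovered, the carried value makes their arm look too poor. If they would have worsened, it makes their arm look too good.

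**Step 3: size of the dilution (first branch only).** Assume that a share *f* of sham patients switches after month *k* (*k* = 1 to 5), and that the standard deviation is unchanged.

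- Six-month average, full effect at once: a switcher has the effect for 6−*k* of 6 months, so the share kept is 1 − *f*(6−*k*)/6.
- Six-month average, effect building evenly (*j*/6 after *j* treatments): the AKA-H arm accumulates 1+2+…+6 = 21 units and a switcher 1+…+(6−*k*), so the share kept is 1 − *f*·[1+…+(6−*k*)]/21.
- Final month, full effect at once: the share kept is 1 − *f*, whatever *k* is.

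For *f* = 10%, the first formula gives 1 − 0.10×5/6 = 0.917 (*k* = 1) and 1 − 0.10×1/6 = 0.983 (*k* = 5). The second gives 1 − 0.10×15/21 = 0.929 and 1 − 0.10×1/21 = 0.995. The third gives 0.90.

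| Share switching | Average, immediate effect (*k* = 1 to 5) | Average, even build-up (*k* = 1 to 5) | Final month, immediate effect |
|---|---|---|---|
| 5% | 95.8–99.2% | 96.4–99.8% | 95% |
| 10% | 91.7–98.3% | 92.9–99.5% | 90% |
| 20% | 83.3–96.7% | 85.7–99.0% | 80% |
| 30% | 75.0–95.0% | 78.6–98.6% | 70% |

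**Step 4: what the last column would mean for power.** Assume two-sided alpha 0.05, 1:1 allocation, a standardised effect of 0.5 (63 per arm) or 0.8 (25 per arm), and about 80% power without switching. A contrast reduced to 1 − *f* then gives power of about 71–72% at 10%, 61–62% at 20% and 50–51% at 30%. These are upper-end losses, because every switcher is credited with the full effect and no time on sham counts.

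**The case against.** The best defence is ethical and practical. Patients have had pain for at least six months without improvement on conservative care, they came seeking AKA-H, and they may face six months of sham. An exit on request is a recognisable trade-off, and such terms go through the ethics committee. A sham patient who is refused a change can withdraw and obtain AKA-H at another listed hospital, which leaves missing data or unrecorded contamination instead of a documented switch. Few patients may ask, and the care taken to keep them unaware of the procedure is meant to limit requests.

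Much of this stands. Deferring the change carries a cost, and a low switching rate would make the dilution small. It does not follow that disclosure on demand is needed. The change criteria already stop therapy on the patient's wish or on deterioration, the consent section protects withdrawal at any time, oral medication and patches may continue, and AKA-H is available after completion.

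Three stronger readings are tempting, and the documents support none of them:

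- *The clause manufactures a benefit for AKA-H.* The dilution runs against AKA-H. The rating bias and the carried-forward values could go either way.
- *Dilution and unblinded ratings are certain to occur.* Both need outcome data collected after the disclosure or switch, and the Protocol does not say whether these are collected.
- *The percentages above measure the damage to this trial.* The switching rates are assumed, and section 6 names no six-month average as the summary.

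**Conclusion.** The point holds as a design weakness that should be fixed. Followed as written, the rule lets the trial's only blind be lifted at the patient's wish during the comparison, for outcomes the patient rates. Either way of handling the data afterwards carries a cost: unblinded ratings plus dilution, or carried-forward values.

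The size cannot be derived from the documents. If 10% of sham patients switch and remain in follow-up, about 92–99.5% of the difference is kept on an assumed six-month average, and 90% at the final month with a full immediate effect. The bias in ratings after disclosure cannot be sized or signed.

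The conclusion rests on reading the change criteria as in-trial rules. That is an inference from the heading, the wording and the separate post-treatment rule, and no other reading gives the clause a purpose.

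**What to change.** Replace the disclosure sentence in the change criteria with text such as:

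> Elective disclosure and change to AKA-H take place only after the seventh-month evaluation (see Post-Treatment Therapy). Earlier unblinding is allowed only for safety or where medical management requires knowledge of the allocation; the date and reason are logged. Patients may stop treatment or withdraw consent at any time. Anyone unblinded, switched or stopping early who has not withdrawn consent is asked to continue the VAS diary, RDQ and SF-36 to the seventh-month evaluation. Observed values are analysed in the randomised arm and are not replaced by carried-forward values.

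The cost is one amended paragraph, ethics approval and revised patient information as section 9 requires, and a log entry for each early unblinding. The downside is that sham patients wait until month 7 for elective AKA-H. Some may withdraw or seek it elsewhere, which exchanges dilution for missing data or contamination. Continued follow-up on all three outcomes is therefore the essential part of the change, although it cannot bind patients who withdraw consent.

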**Post-Treatment Therapy**

Once the test is complete, disclosure is made to the patients as to whether they had AKA-H treatment or Sham treatment, and patients are asked if they wish to continue treatment. If treatment was Sham, patients were allowed to change treatment to AKA, and if treatment was AKA-H, patients could continue with AKA-H.

**Safety Considerations**

Facilities in every area of Japan are using this treatment method, and although these facilities are not great in number, there have been no reports of any serious adverse events to the treatment as of yet.

**Possible Adverse Events**

- Mild low back pain or lower leg numness is reported; patient is to report immediately by phone if this type of symptom occurs, and is recommended to come in to the hospital as soon as possible.
- Patient is examined as needed upon arrival at hospital, continuation of treatment is determined based on consultation with patient.

**Reporting Procedures for Adverse Events**

In the event of any serious adverse events, the person in charge of the research shall report to the head of the hospital and to the AKA Medical Society, and appropriate treatment shall be taken.

**5. Outcomes and Confidentiality**

Primary outcome and secondary outcomes

- Primary outcome is mean VAS score over a month from the previous visit.
- Participants are required to record their VAS score in a form every day at almost the same time for at least 1 month until the first visit and bring the recorded form along with consent form at the first visit.
- Secondary outcomes are Roland-Morris Disability Questionnaire (RDQ) and 36-Item Short-Form Health Survey (SF-36).
- Participants will fill RDQ and SF-36 at every visit including the first visit at the waiting room by advance reservation only before seeing a doctor. Participants are required to visit the outpatient office once a month, in principle, for 6 months after initiation of treatment.
- A VAS record form will be collected at every visit, and a new one will be provided to the participants.
- RDQ and SF−36 will be filled at the waiting room and will be collected at every visit. Those collected record forms will be stored in the locked locker at outpatient department.

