**6. Statistical Analysis**

- All statistical analyses were performed using the principle of intention-to-treat analysis.
- For missing data, the data were analyzed by extrapolating the last observation.
- A two-way (time period and treatment group) repeated measures analysis of variance will be used to observe the difference in data between the two groups during the intervention period.

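### The primary outcome names no month or summary, and neither between-arm term of its two-way ANOVA is named as the deciding test

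*Protocol*

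**What the plan says.** The protocol's section 5 defines the primary variable: "Primary outcome is mean VAS score over a month from the previous visit". Patients also record daily VAS "for at least 1 month until the first visit", which gives a pre-treatment month. The same section adds: "A VAS record form will be collected at every visit, and a new one will be provided to the participants".

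The schedule in section 4 (Duration and Frequency) reads: "Outpatient treatment shall be once a month for six months, with evaluation in the seventh month". Section 3 describes the comparison as running over the whole six months: "This study was a parallel group comparison in which the AKA-H group and S group were compared for 6 months".

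Section 6 gives the analysis: "A two-way (time period and treatment group) repeated measures analysis of variance will be used", with the purpose "to observe the difference in data between the two groups during the intervention period".

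The protocol gives no primary month, no average or change score, no deciding ANOVA term, no role for the pre-treatment month and no significance level.

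**The concern.** A primary outcome should lead to one between-arm comparison. Here the variable repeats monthly, and the analysis yields three F tests. The time effect does not compare treatments. The group effect and the group-by-time interaction both do, and each could be reported as showing that AKA-H works.

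The two terms answer different questions, and their meaning depends on whether the pre-treatment month is a level of the time factor:

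- **If it is a level,** the group term averages in a month in which no treatment effect can exist, so the effect is diluted. A sustained effect then also appears as an interaction.
- **If it is left out,** a constant effect produces no interaction at all and only the group term can detect it. The collected baseline is then not used.

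The same data could therefore lead to opposite conclusions under two readings of one sentence. Only the patients are blinded in this trial (section 3), so fixing the decision in advance is an important safeguard against choosing the favourable term later.

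**Working it through.** The protocol states no sample size, alpha, SD or effect size, so it has no figure to reproduce.

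**Inputs from the protocol.** There are two arms. Six monthly treatments with evaluation in the seventh month give six post-treatment means, or seven time levels if the pre-treatment month is included.

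**Assumed inputs.** Each test is at 5%. For error rates: 30 and 90 per arm, with correlation between monthly means either constant (0.5, 0.7, 0.9) or AR(1) (0.7, 0.9). For power: 40 per arm, a constant 10 mm effect and SD 20-25 mm.

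**1. False-positive rate if either between-arm term may count.** With normal data and constant correlation the two tests are independent under the null:

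1 − 0.95² = 0.0975, about 10%.

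At 2.5% per test, 1 − 0.975² = 0.0494. Whether 5% is exceeded therefore depends on an alpha that the protocol does not state.

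Null simulation (20,000 trials per setting, six and seven time levels, interaction uncorrected):

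| Decision rule | Constant correlation | AR(1) 0.7-0.9 |
|---|---|---|
| Group term only | about 5% | about 5% |
| Interaction only | about 5% | 7.4-10.0% |
| Either term | 9.4-10.0% | 11.5-14.4% |

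**2. Dilution of the group term.** With the pre-treatment month as one of seven levels, a constant 10 mm effect becomes 10 × 6/7 = 8.57 mm.

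**3. Power.** For constant correlation ρ, the mean of k months has variance SD² × v, with v = (1 + (k − 1)ρ)/k. The standard error of the arm difference is SD × √(v × 2/40). Adjusting the six-month mean for baseline replaces v by v − ρ². Power is for a two-sided 5% t test.

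With ρ = 0.6 (assumed):

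| Analysis | v | Effect | SE (SD 20; 25) | Effect/SE | Power |
|---|---|---|---|---|---|
| Group term, 7 levels | 4.6/7 = 0.657 | 8.57 | 3.63; 4.53 | 2.36; 1.89 | 65%; 46% |
| Group term, 6 levels | 4/6 = 0.667 | 10 | 3.65; 4.56 | 2.74; 2.19 | 77%; 58% |
| Six-month average, baseline-adjusted | 0.667 − 0.36 = 0.307 | 10 | 2.48; 3.10 | 4.04; 3.23 | 98%; 89% |

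The low ends of the ranges come from other assumed correlations, at SD 25:

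- **Correlation falling from 0.76 to 0.43, group term with seven levels.** Here v = 0.70, SE = 25 × √(0.70 × 0.05) = 4.68 and 8.57/4.68 = 1.83, so power is 44%.
- **AR(1) 0.8, adjusted contrast.** The six-month mean has v = 0.680 and its mean correlation with baseline is 0.492. Then 0.680 − 0.492² = 0.438, SE = 25 × √(0.438 × 0.05) = 3.70 and 10/3.70 = 2.70, so power is about 75%.

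Over these settings the adjusted contrast has about 75-98% power and the unadjusted group term about 44-77%. In simulation the interaction has about 40-70% with baseline as a level and about 5-9% without it.

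These ranges are not bounds. With ρ = 0.5 and SD 20, the six-level group term has v = 3.5/6 = 0.583, SE 3.42 and power 82%. The adjusted contrast has v = 0.333, SE 2.58 and power 97%. The ordering is unchanged.

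**The case against.** The best defence is that section 6 limits the aim to the between-group difference during the intervention period. That reads most naturally as the group term over the treatment months. On that reading there is one test, and at 5% its error rate is 5%. This is fair, and the proposed contrast keeps that aim. But the wording does not exclude the interaction and does not settle whether the pre-treatment month is a level of time.

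It may also be said that the analysis plan, which is not shown, could settle the matter. That holds for a sphericity correction or a covariance structure. It does not hold for the primary month or contrast, which belongs in the protocol.

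Three stronger readings are tempting, and the documents do not support them:

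- **That the false-positive rate exceeds 5%.** The protocol states neither an alpha nor a rule that either term suffices.
- **That the interaction test is necessarily anti-conservative.** This assumes no sphericity correction. Under correlation falling from 0.76 to 0.43, a Greenhouse-Geisser correction brings the interaction's error rate to about 4.9%.
- **That any single visit may count as success.** No per-visit tests are announced.

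It is also true that the power gain does not come from naming a contrast alone. In the first power table, leaving baseline out of the time factor takes 65% to 77% at SD 20, and adjusting for it takes 77% to 98%.

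**Conclusion.** The point holds as an ambiguity in the primary analysis and should be fixed. The protocol fixes no primary month or summary, does not say which of two between-arm terms decides, and leaves the role of the pre-treatment month open.

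The size is conditional. If either term may count at an assumed 5% each, the false-positive rate is about 10%, rising to about 11-14% if the interaction is uncorrected and correlation falls with time. With one named group contrast at 5% it is about 5%. The power advantage of the adjusted contrast (about 75-98% against about 44-77%) rests on the assumed 40 per arm, constant 10 mm effect, SD 20-25 mm and correlations shown, none of which is in the protocol. A reader might infer an error rate already inflated by design, but the text shows an open choice, not a rule that inflates it.

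**What to change.** In sections 5 and 6, name one primary contrast: the AKA-H minus sham difference in monthly mean VAS, averaged over the post-treatment months and adjusted for the pre-treatment monthly mean. Test it two-sided at 5% and report it with a 95% CI. State that the pre-treatment month is a covariate and not a level of time, and that the group-by-time and single-month comparisons are supportive.

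No particular covariance model or degrees-of-freedom method is needed to cure the defect.

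The cost is a change of wording, submitted as a protocol change under section 9. It needs no new visits or data, because the pre-treatment diary is already collected. The downside for the sponsor is giving up the choice of term after seeing the data. An effect that appears only late would also be diluted in the average and would show mainly in the supportive comparisons.
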